## **5. STUDY POPULATION**

### **5.1. Number of Subjects**

20 subjects will be randomized to receive the treatments in the assigned sequences. In case the number of evaluable subjects, who complete all dosing and critical assessments, in any treatment group is less than 10 due to early withdrawal, the decision to replace will be made at the discretion of the Sponsor and Investigator so as to ensure at least 10 evaluable subjects per treatment group.

### **5.2. Eligibility Criteria**

#### **5.2.1. Inclusion Criteria**

Deviations from inclusion criteria are not allowed because they can potentially jeopardize the scientific integrity of the study, regulatory acceptability or subject safety. Therefore, adherence to the criteria as specified in the protocol is essential.

A subject will be eligible for inclusion in this study only if all of the following criteria apply:

1. Healthy male or females aged 18 - 45 years, inclusive, and the ratio of male and female is 1:1. Healthy as determined by a responsible and experienced physician, based on a medical evaluation including medical history, physical examination, laboratory tests and cardiac monitoring.
2. Body weight  $\geq 50\text{kg}$  and body mass index ( $\text{weight}/\text{height}^2$ ) within the range of 19 - 24  $\text{kg}/\text{m}^2$ , inclusive.
3. Male or female subjects at the time of signing the informed consent:
  - Female subject who is child-bearing potential should agree to use one of the contraception methods listed in Section 8.1.1. (contraceptives intrauterine device, implantable progesterone device or oral contraceptive) for an appropriate period of time (as determined by the product label or investigator) prior to the start of dosing to sufficiently minimize the risk of pregnancy at that point. The subjects must agree to use contraception until completion of the follow-up visit.
  - Male subjects have to agree to use one of the contraception methods listed in Section 8.1.2. This criterion is to be followed from the time of the first dose of study medication until completion of the follow-up visit
4. Normal systolic (90-139mmHg) and diastolic (60-89mmHg) blood pressure at pre-study screening.
5. Subjects who are current non-smokers, who have not used any tobacco products in the 6 month period preceding the screening visit, and have a pack history of  $\leq 10$  pack years. (pack years = (cigarettes per day smoked/20)  $\times$  number of years smoked)).

6. No significant abnormality on 12-lead ECG at screening, QTcF interval must be <450msec (QTcF; machine or manual reading).
7. AST (SGOT), ALT (SGPT), and total-bilirubin  $\leq 1.5 \times \text{ULN}$  at screening. No significant clinical abnormality on other laboratory tests.
8. Capable of giving written informed consent, which includes compliance with the requirements and restrictions listed in the consent form.
9. Subjects who are able to use the inhalation device satisfactorily

### **5.2.2. Exclusion Criteria**

Deviations from exclusion criteria are not allowed because they can potentially jeopardize the scientific integrity of the study, regulatory acceptability or subject safety. Therefore, adherence to the criteria as specified in the protocol is essential.

A subject will not be eligible for inclusion in this study if any of the following criteria apply:

1. As a result of medical interview, physical examination or screening investigations, the principle investigator or delegate physician deems the subject unsuitable for the study.
2. History of mental, cardiac, renal, hepatic, significant gastrointestinal or respiratory disease as judged by the investigator
3. A history of breathing problems (i.e. history of asthmatic symptomatology, unless asthma in childhood that has now resolved and no longer requires maintenance therapy which should not be an exclusion).
4. A chest X-ray or computed tomography (CT) scan that reveals evidence of clinically significant abnormalities. A chest X-ray must be taken at day -1 of the first treatment if a chest X-ray or CT scan is not available within 6 months prior to that day.
5. History of sensitivity to heparin, heparin-induced thrombocytopenia, or sensitivity to any of the study medications, or components thereof, known allergy or hypersensitivity to milk protein or the excipients lactose monohydrate and magnesium stearate (MgSt), or a history of drug or other allergy that, in the opinion of the investigator or GSK Medical Monitor, contraindicates their participation.
6. The subject has taken prescription or non-prescription drugs, including CYP3A/PGP inhibitor, vitamins, herbal and dietary supplements (including St John's Wort) within 7 days (or 14 days if the drug is a potential enzyme inducer) or 5 half-lives (whichever is longer) prior to the first dose of study medication, unless in the opinion of the Investigator and Sponsor the medication will not interfere with the study procedures or compromise subject safety.
7. Positive result of urine cotinine test.
8. The subject has a history of cholecystectomy or biliary tract disease.

9. The subject has a significant clinical history or current conditions of glaucoma.
10. The subject has a significant clinical history or current conditions of prostatic hypertrophy.
11. The subject has a positive pre-study drug screen. A minimum list of drugs that were screened for included amphetamines, barbiturates, cocaine, opiates and benzodiazepines. The detection of drugs with a legitimate medical use was not necessarily an exclusion to study participation. The detection of alcohol was not an exclusion at screening but had to be negative pre-dose and during the study.
12. History of regular alcohol consumption within 3 months of the study defined as:
  - Abuse of an average weekly intake of greater than 21 units or an average daily intake of greater than three units (males), or defined as an average weekly intake of greater than 14 units or an average daily intake of greater than two units (females). One unit was equivalent to a half-pint (220 mL) of beer or one (25 mL) measure of spirits or one glass (125 mL) of wine.
13. Female subjects, who are pregnant, planned pregnancy or lactation.
14. The subject has participated in a clinical trial and has received an investigational product within the following time period prior to the first dosing day in the current study: 30 days, 5 half-lives or twice the duration of the biological effect of the investigational product (whichever is longer).
15. Blood donation or sampled as a study subject within three months preceding the first dose of study drug and blood donation during the entire study in excess of 500mL.
16. A positive pre-study Hepatitis B surface antigen or positive Hepatitis C antibody result within 3 months of screening.
17. The subject has tested positive for HIV antibodies.
18. Unwillingness or inability to follow the procedures outlined in the protocol.
19. Subject is mentally or legally incapacitated.

### **5.2.3. Other Eligibility Criteria Considerations**

To assess any potential impact on subject eligibility with regard to safety, the investigator must refer to the following document(s) for detailed information regarding warnings, precautions, contraindications, adverse events, and other significant data pertaining to the investigational product(s) being used in this study:

- GSK573719+GW642444 IB [GlaxoSmithKline Document Number [RM2009/00437/02](#)].
- GSK573719 IB [GlaxoSmithKline Document Number [RM2006/00835/08](#)].
- GW642444 IB [GlaxoSmithKline Document Number [SM2003/00028/09](#)].

## **6. DATA ANALYSIS AND STATISTICAL CONSIDERATIONS**

### **6.1. Hypotheses and Treatment Comparisons**

The primary objective of this study is to evaluate the pharmacokinetics of UMEC (62.5µg and 125µg) and VI (25µg) administered as single and repeat inhaled doses and in combinations of UMEC/VI (62.5g/25µg) and UMEC/VI (125µg/25µg) in healthy Chinese subjects. No formal hypothesis tests are planned, and an estimation approach will be adopted.

The primary comparisons of interest between treatment regimens (see Section 4.1) include:

- (1) Effect of co-administration of 25µg VI on the UMEC PK exposure (e.g. AUC and Cmax) following single and repeat doses of UMEC:
  - a. Treatment A vs C on Day 1 and Day 10
  - b. Treatment B vs D on Day 1 and Day 10
- (2) Effect of co-administration of at 62.5µg or 125µg UMEC on the VI PK exposure following single and repeat doses of GSK642444:
  - a. Treatment A vs E on Day 1 and Day 10
  - b. Treatment B vs E on Day 1 and Day 10

Point estimates and corresponding 90% confidence intervals will be presented for each treatment comparison.

### **6.2. Sample Size Considerations**

#### **6.2.1. Sample Size Assumptions**

There is no formal hypothesis testing in this estimation approach driven study. This study is to evaluate the pharmacokinetics of UMEC and VI as monotherapies and concurrently in healthy Chinese subjects for the first time. Sample size is driven by feasibility as well as the requirement from Chinese regulatory agency (SFDA). A total of 20 healthy subjects aged 18-45 years will be randomised into the study. In case the number of evaluable subjects in any treatment group is less than 10 due to early withdrawal, the decision to replace will be made at the discretion of the Sponsor and Investigator so as to ensure at least 10 evaluable subjects per treatment group.

#### **6.2.2. Sample Size Sensitivity**

The above sample size is chosen to meet SFDA's requirement for PK studies. No sample size sensitivity analysis will be performed.

### **6.2.3. Sample Size Re-estimation**

No sample size re-estimation will be performed.

## **6.3. Data Analysis Considerations**

### **6.3.1. Interim Analysis**

No formal interim analysis is planned.

### **6.3.2. Final Analyses**

#### **6.3.2.1. Analysis Population**

##### **Safety population**

All subjects who receive at least one dose of study medication will be included in the safety population.

##### **PK population**

The PK Population is defined as all subjects in the Safety Population for whom a PK sample was obtained and analyzed.

#### **6.3.2.2. Pharmacokinetic Analyses**

##### **6.3.2.2.1. Raw Plasma Concentrations**

Linear and semi-logarithmic individual plasma concentration-time profiles and mean and median profiles of UMEC and VI by treatment group and day (Day 1 and Day 10) will be plotted. Plasma concentrations of UMEC and VI will be listed and summarized by treatment, day and nominal time, according to the PK Population.

Plasma concentration time data for UMEC and VI will be analyzed by non-compartmental methods with WinNonlin [version 4.1 or higher]. Calculations will be based on the actual sampling times recorded during the study.

##### **6.3.2.2.2. Derived Plasma Pharmacokinetic Parameters**

From the concentration-time data, the following pharmacokinetic parameters will be determined for each single dose of UMEC and VI:  $C_{max}$ ,  $t_{max}$ ,  $t_{last}$ , and  $AUC_{0-t}$ . Other parameters such as  $t_{1/2}$ ,  $AUC_{0-\infty}$ ,  $CL/F$ ,  $Vd/F$  may be derived if data permits. If  $AUC_{0-\infty}$  is noncalculable,  $AUC_{0-t'}$  will be derived with  $t'$  being the latest time at which concentration is  $>NQ$  within each analyte across all subjects and treatments (for example  $AUC_{0-4}$  or  $AUC_{0-8}$  etc).

The following pharmacokinetic parameters will be determined from the plasma concentration-time data following repeated doses of UMEC and VI:  $C_{\max}$ ,  $t_{\max}$ ,  $t_{\text{last}}$ ,  $AUC_{0-t}$ , and as data permit: terminal phase half life ( $t_{1/2}$ ),  $C_{\tau}$ ,  $AUC_{0-\tau}$ ,  $R_o$  and  $RC_{\max}$ , DF. If  $AUC_{0-\tau}$  is noncalculable,  $AUC_{0-t'}$  will be derived with  $t'$  being the latest time at which concentration is >NQ within each analyte across all subjects and treatments (for example  $AUC_{0-4}$  or  $AUC_{0-8}$  etc).

If  $C_{\max}$  is not calculable, it will be imputed with  $\frac{1}{2}$  the lower limit of quantification prior to calculating summary statistics. If AUC parameters are not calculable, they will be imputed with  $\frac{1}{2}$  the lowest calculable AUC within each analyte across all subjects and treatments. None of the other parameters will be imputed.

All derived pharmacokinetic parameters will be listed and summarized by treatment and day according to the PK Population.

#### **6.3.2.2.3. Steady State**

A plot of median trough plasma UMEC and VI concentrations on Day 6 to Day 10, as well as 24h post dose on Day 10 (Day 11) by treatment group (Linear and semi-log) and a plot of individual trough plasma UMEC and VI concentrations will be produced to visually inspect when steady state is achieved.

To formally evaluate whether steady state is achieved, statistical analysis of pre-dose concentration levels after log-transformation of the data on Day 6 to Day 10 as well as 24 hours post dose on Day 10 (Day 11) will be conducted for UMEC and VI separately. A mixed effect ANOVA model will be fit with treatment, day (as a continuous covariate) and treatment\*day as a fixed effect and subject as a random effect for each analyte separately. The slope coefficient and the associated 90% confidence intervals will be derived to evaluate whether steady state is achieved.

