### 4. INVESTIGATIONAL PLAN

#### 4.1. Study Design/Schematic

This is a single centre, randomized, open label, 3-period crossover, balanced incomplete block study in healthy Chinese subjects.

All subjects will attend the unit for screening within 21 days of their first of three dosing periods. Each subject will receive three of the five treatment regimens described in [Table 1](#) below.

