## **4.3. Treatment Assignment**

Subjects will be assigned to three-period incomplete cross-over treatment sequence in accordance with the randomization schedule generated by GlaxoSmithKline Biometrics, GlaxoSmithKline R&D, prior to the start of the study, using validated internal software. A replacement schedule will also be set up in place along the randomization schedule in case of a decision made to replace an early withdrew subject.

Prior to the start of the study, 20 subjects will be randomly assigned to one of 20 possible treatment sequences with the aim to achieve 10-12 evaluable subjects for each regimen. A description of each regimen is provided in [Table 1](#). The 20 sequences are based on a balanced incomplete block design. In this design as described below, both treatment and possible pair of treatments occur across periods evenly:

| Sequence | Period 1 | Period 2 | Period 3 |
|----------|----------|----------|----------|
| 1        | A        | E        | D        |
| 2        | B        | A        | E        |
| 3        | C        | B        | A        |
| 4        | D        | C        | B        |
| 5        | E        | D        | C        |
| 6        | A        | B        | C        |
| 7        | B        | C        | D        |
| 8        | C        | D        | E        |
| 9        | D        | E        | A        |
| 10       | E        | A        | B        |
| 11       | A        | D        | B        |
| 12       | B        | E        | C        |
| 13       | C        | A        | D        |
| 14       | D        | B        | E        |
| 15       | E        | C        | A        |
| 16       | A        | C        | E        |
| 17       | B        | D        | A        |
| 18       | C        | E        | B        |
| 19       | D        | A        | C        |
| 20       | E        | B        | D        |

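### The steady-state model has a random subject effect only, although each subject gives up to three trough series, so the slope's 90% CI does not in general have its nominal coverage

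*Protocol*

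**What the plan says.** Section 4.1 makes this a three-period crossover: "Each subject will receive three of the five treatment regimens". Section 4.3 lists the sequences: "20 subjects will be randomly assigned to one of 20 possible treatment sequences with the aim to achieve 10-12 evaluable subjects for each regimen".

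Section 6.3.2.2.3 plans trough plots for visual inspection and then a formal model for each analyte, on "log-transformation of the data on Day 6 to Day 10 as well as 24 hours post dose on Day 10 (Day 11"). The fixed part is given as "A mixed effect ANOVA model will be fit with treatment, day (as a continuous covariate") and treatment-by-day. The random part is "as a fixed effect and subject as a random effect for each analyte separately". The result is used as follows: "The slope coefficient and the associated 90% confidence intervals will be derived to evaluate whether steady state is achieved". The section states no rule for reading the interval.

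Sections 6.3.2.2.4 (accumulation) and 6.3.2.2.6 (treatment comparison) leave model details to the Reporting and Analysis Plan. Section 6.3.2.2.3 does not; it fixes its model in the protocol.

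**The concern.** Each subject-period yields its own six-point trough series, separated from the next by a washout and taken on a different regimen. A single random subject intercept treats all of a subject's troughs, given treatment and day, as equally correlated, whichever period they come from. Two sources of variation then have no term of their own: the shift in a subject's level from one period to the next, and differences in slope between series.

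Both fall into the residual, and the residual sets the standard error of the slope. A level shift does not belong there, because with complete series it does not affect the slope estimate. A slope difference belongs in the standard error in full, but reaches it only in diluted form. The stated 90% interval is the numerical basis for the steady-state assessment, so its coverage matters for how that assessment is read.

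**Working it through.** **1. Count the series (Section 4.3 sequence table).** 20 subjects × 3 periods / 5 regimens = 12 per regimen, which is the upper end of the stated 10-12.
- UMEC (regimens A-D): the 12 subjects who receive E give 2 series each and the other 8 give 3. 12×2 + 8×3 = 48 series, 288 troughs.
- VI (A, B, E): 6 subjects give 1 series, 12 give 2 and 2 give 3. 6 + 24 + 6 = 36 series, 216 troughs.

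**2. True standard error of a regimen's slope.** For Days 6-11 the sum of squares about the mean day is 17.5. Let σ be the residual SD, p the period-to-period SD of a series' level and b the SD of slopes between series, all on the log scale. With complete series the slope does not depend on level, so

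SE_true = √[(b² + σ²/17.5)/12].

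**3. Standard error that the stated model reports.** The residual absorbs p and b in proportion to their degrees of freedom:

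residual ≈ σ² + 6p²·(f_L/f_R) + 17.5b²·(f_S/f_R), and SE_model = √[residual/(12×17.5)].

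- UMEC: f_L = 48−20−3 = 25; f_S = 48−4 = 44; f_R = 288−20−3−4 = 261.
- VI: f_L = 36−20−2 = 14; f_S = 36−3 = 33; f_R = 216−20−2−3 = 191.

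**4. Numbers.** The protocol gives no variance components. Assumed: σ = 0.2, with p from 0 to 0.3 and b from 0 to 0.10 per day.

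| p | b | UMEC SE_model | SE_true | UMEC ratio | UMEC coverage of the 90% CI | VI ratio |
|---|---|---|---|---|---|---|
| 0 | 0 | 0.0138 | 0.0138 | 1.00 | 0.90 | 1.00 |
| 0.1 | 0 | 0.0148 | 0.0138 | 1.07 | 0.92 | 1.05 |
| 0.2 | 0 | 0.0173 | 0.0138 | 1.25 | 0.96 | 1.20 |
| 0.3 | 0 | 0.0209 | 0.0138 | 1.51 | 0.99 | 1.41 |
| 0.1 | 0.05 | 0.0159 | 0.0200 | 0.80 | 0.81 | 0.79 |
| 0.2 | 0.05 | 0.0183 | 0.0200 | 0.92 | 0.87 | 0.88 |
| 0.2 | 0.10 | 0.0210 | 0.0320 | 0.66 | 0.72 | 0.64 |

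Example, UMEC with p = 0.2 and b = 0: residual = 0.04 + 6×0.04×25/261 = 0.0630; SE_model = √(0.0630/210) = 0.0173; ratio = 0.0173/0.0138 = 1.25.

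**5. Check by simulation.** REML fits of the stated model on the 20 sequences (between-subject SD 0.3) gave UMEC ratios of 1.06, 1.26 and 1.51 for level shifts only. With b = 0.05 they gave 0.78 to 0.91, with coverage 0.80 to 0.85. Day-to-day correlation of 0.5 within a series, without slope variation, gave 0.83 to 0.85 at p = 0.1 and 0.95 to 1.03 at p = 0.2 over both analytes.

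**6. Where the sign changes.** Setting SE_model = SE_true for UMEC gives b² = p²·(6×25/261)/[17.5×(1−44/261)], so b ≈ 0.20p. That is about 0.04 per day at p = 0.2 and 0.06 per day at p = 0.3. Below this the interval is too wide; above it, too narrow.

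**7. What restores coverage.** A series intercept alone does so when only levels differ. With b = 0.05 its simulated coverage was 0.76 to 0.81. Taking one slope per series, and the interval from the between-series variation of slopes within regimen (44 degrees of freedom for UMEC, 33 for VI), gave simulated coverage of 0.90 for both analytes with b = 0, 0.05 and 0.10 and also with correlation 0.5. That analysis does not depend on p.

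**The case against.** The strongest objection concerns direction. A reader might infer that the interval is always too wide, and that this makes steady state easier to conclude. The documents support neither step. The first needs series that differ in level but hardly in slope, and the protocol gives no variances to settle that; step 6 shows how small a slope variation reverses the sign. The second needs a rule that steady state is concluded when the interval includes zero. Section 6.3.2.2.3 states no such rule, and Section 6.1 says that no formal hypothesis tests are planned and that estimation is the approach. If the change had to lie within limits, a wider interval would work against concluding steady state.

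A reader might also infer that every Day 10 comparison and the accumulation ratio Ro depend on this result. They do not. Section 6.1 compares regimens on the same day after the same duration of dosing, and Ro in Section 6.3.2.2.4 is an observed Day 10 to Day 1 ratio.

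Three further points stand. The sizes rest on assumed variances, and with no period-to-period variation in level or slope there is no distortion. The trough plots give an assessment that does not use the model. The calculations assume complete series, whereas Sections 6.3.2.2.2 and 6.3.2.2.4 anticipate concentrations below quantification. None of this removes the omission: the protocol itself fixes the random structure, and that structure does not match the design.

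**Conclusion.** The point holds as one of calibration. The stated model omits the subject-by-period level and series-specific slopes, so the slope's 90% interval does not in general cover 90%. At an assumed residual log-SD of 0.2, the UMEC standard error runs from about 1.5 times the true value (levels differ with SD 0.3, slopes equal) down to about 0.8 times (level SD 0.1, slope SD 0.05 per day). VI behaves alike, with slightly less inflation. The interval is close to nominal only when both variances are negligible or when the two errors happen to offset.

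The direction cannot be stated in advance, and no bias toward concluding steady state is shown. With complete series the slope estimates themselves are unaffected. Confidence is high on the omission and conditional on its size. The text should be changed, since the change is small and the section presents this as its formal assessment.

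**What to change.** In Section 6.3.2.2.3, replace the random subject effect alone with random subject plus a random intercept and a random day slope at subject-by-period level. Make this the primary model, not an option. Equivalently, for complete series, estimate one slope per series and base the interval on the between-series variation of slopes within regimen. If the slope variance is estimated at zero, the model reduces to the subject-by-period intercept.

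Report each slope as percent change per day and as cumulative change over Days 6 to 11, with its 90% interval. State that steady state is judged by the size of that change, not by whether the interval includes zero.

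A fixed period term is optional: period is constant within a series, and the sequences are balanced at 4 subjects per regimen per period.

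The cost is a few lines of protocol text and no new data. The only downside is somewhat wider intervals when slopes do vary, which then reflect the real uncertainty.
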